# Effect of add-on therapy with leukotriene receptor antagonists and Chungsangboha-tang in patients with asthma: a protocol for a randomized, placebo-controlled, parallel, multicenter trial

**DOI:** 10.1186/s12906-025-04799-w

**Published:** 2025-02-14

**Keywords:** Asthma, Chungsangboha-tang, Herbal medicine, Korea traditional medicine, Leukotriene receptor antagonists

## Abstract

**Background:**

Asthma is a chronic disease characterized by airway inflammation and obstruction. Treatment aims to control symptoms with minimal medication, using disease-controlling and symptom-relieving drugs. Inhaled steroids and beta2 agonists are common treatments; however, their long-term use can cause side effects. Leukotriene receptor antagonists (LTRAs) are used in combination with inhaled steroids to manage asthma because of their anti-inflammatory and bronchodilatory effects. Combining LTRAs with Chungsangboha-tang (CSBHT), a Korean medicine, may enhance their efficacy. This study aimed to evaluate the potential of CSBHT as an adjunctive therapy for asthma management in a randomized, placebo-controlled, double-blind, multicenter clinical trial.

**Methods:**

This randomized, placebo-controlled, double-blind, parallel-group, multicenter study aims to evaluate the efficacy and safety of CSBHT as an additional treatment for patients with asthma, particularly for those with LTRAs. Overall, 198 participants will be randomly divided into intervention and control groups, with the former receiving CSBHT thrice daily and the latter receiving a placebo. Follow-ups at weeks 0, 4, and 8 will include outcome measurements, medication dispensation, and adverse reaction monitoring. The primary outcome is the mean change in forced expiratory volume in one-second scores, with secondary outcomes including changes in peak expiratory flow, forced vital capacity, forced expiratory flow 25–75%, fractional exhaled nitric oxide, Asthma Control Test, Asthma Quality of Life Questionnaire, serum IgE, eosinophil count, C-reactive protein, rescue medication usage, and a descriptive analysis of the questionnaire on asthma symptoms in Korean medicine. Safety assessments will be conducted using laboratory tests, vital signs, and monitoring of adverse events. Economic evaluations will be conducted using either cost-minimization analysis or cost-utility analysis.

**Discussion:**

This trial will evaluate the efficacy, safety, and cost-effectiveness of CSBHT as an add-on therapy to LTRAs to establish its potential as an adjuvant therapy in asthma management.

**Trial registration:**

This study was registered in the Clinical Research Information Service of Korea (KCT0006005), on March 16, 2021.

## Introduction

Asthma is a persistent and challenging chronic inflammatory disease of the airways, characterized by the hypersecretion of airway mucus, airway obstruction, eosinophilic airway inflammation, and airway hyperresponsiveness [1]. While it remains an intractable condition without a cure, the primary goal of asthma management is to achieve optimal control with minimal risk [2]. Therapeutic drugs for asthma can be categorized into two main classes: controller medications, which are employed to mitigate symptoms through their anti-inflammatory effects; and reliever medications, which are reserved for symptom alleviation during acute episodes by rapidly dilating the airways [2].

Leukotriene receptor antagonists (LTRAs), which include montelukast, pranlukast, and zafirlukast, are utilized in conjunction with inhaled steroids to manage asthma due to their anti-inflammatory effects, bronchodilatory properties, ability to reduce cough, improve lung function, alleviate airway inflammation, and decrease asthma exacerbations [3]. While LTRAs are less effective than inhaled corticosteroids (ICSs) [4], the 2024 GINA guideline suggests that they can be adopted as a maintenance method as an alternative to increasing ICS dosage [2]. The addition of LTRAs in patients already on ICS or ICS-long-acting beta2 agonist (LABA) is beneficial in controlling asthma, preventing exacerbations, and improving lung function; however, the benefits are limited and not applicable in all populations [5–7]. Consequently, there is a growing interest in the use of supplementary medications for asthma management.

Chungsangboha-tang (CSBHT) is a traditional medicine composed of 18 different drugs that have been widely used to treat respiratory diseases in East Asian countries. In vitro, animal, and human studies conducted in Korea have reported that CSBHT is clinically effective in treating asthma because of its anti-inflammatory and immunomodulatory actions [8]. Therefore, it could be a beneficial therapeutic option, complementing standard asthma treatments with its unique efficacy.

Here, we suggest that combining LTRAs with CSBHT may enhance the effectiveness of LTRAs in controlling asthma. In this study, we aim to establish the potential of CSBHT as an adjunctive therapy for asthma management by evaluating its efficacy, safety, and cost-effectiveness as an add-on therapy to LTRA in a randomized, placebo-controlled, double-blind, parallel-group, multicenter clinical trial. This study used a placebo that corresponds 1:1 to CSBHT as a control, as the placebo is the most stringent method for testing therapeutic efficacy and it is a method that can evaluate the real additional efficacy for add-on treatments to standard therapy [9]. With this study, we hope to present a standardized treatment approach that may pave the way for future health insurance coverage.

## Methods and analysis

### Trial design

This clinical trial is a randomized, placebo-controlled, double-blind, parallel-group, multicenter study that aims to ascertain the efficacy and safety of applying a treatment method that adds CSBHT to patients with asthma, a common refractory airway disease, who have received standard treatment at each stage, particularly those administered LTRAs. The study plans to recruit participants from the Department of Pulmonology and Allergy of Kyung Hee University Hospital and Inha University Hospital in South Korea, targeting patients with asthma receiving standard treatment. The clinical trial will be conducted at the Clinical Trial Centers of Kyung Hee University Korean Medicine Hospital, Inha University, Pusan National University Korean Medicine Hospital, Daejeon University Korean Medicine Hospital, and Semyung University Korean Medicine Hospital. After explaining the clinical trial to the participants, screening will be conducted on participants for whom consent has been obtained. A total of 198 participants who meet the inclusion and exclusion criteria will be recruited as research subjects and will then be randomly assigned to the intervention and control groups in a 1:1 ratio. The intervention group will take one packet of CSBHT thrice a day, and the placebo group will take one packet of CSBHT placebo thrice a day. Participants will visit after the screening visit at 0, 4, and 8 weeks, where they will receive their medication in two separate dispensations, one at 0 weeks and the other at 4 weeks. At each visit, evaluations for this study will take place, which will encompass monitoring for adverse reactions. This research protocol complies with the Good Clinical Practice guidelines, the Helsinki Declaration, and the Standard Protocol Items: Recommendations for Interventional Trials (SPIRIT) statement. This clinical trial has been registered with the Clinical Research Information Service (https://cris.nih.go.kr/cris/en/) under registration number KCT0006005.

Figure 1 presents the research flow, while Table 1 outlines the research schedule.

**Fig. 1 Fig1:**
[figure not shown]
Study flow chart

**Table 1 Tab1:**
[figure not shown]
Timeline for the study protocol

*CSBHT* Chungsangboha-tang, *ECG* electrocardiogram, *FeNO* fractional exhaled nitric oxide, *ACT* Asthma Control Test, *AQLQ* Asthma Quality of Life Questionnaire, *EQ-5D* EuroQol 5-dimension, *CRP* c-reactive protein, *AST* aspartate aminotransferase, *ALT* alanine aminotransferase, *ALP* alkaline phosphatase, *TB* total bilirubin, *GGT* gamma glutamyl transferase, *BUN* blood urea nitrogen, *Na* sodium, *K* potassium, *Cl* chloride, *WBC* white blood cell count, *RBC* red blood cell count, *eGFR* estimated glomerular filtration rate

^*^Screening tests should be conducted within 7 days prior to Visit 1 (0 weeks), and laboratory assessments including AST, ALT, ALP, TB, GGT, BUN, creatinine, Na, K, Cl, WBC, RBC, hemoglobin, hematocrit, and platelet count should be confirmable on Visit 1. For suitable candidates, Screening and Visit 1 can be conducted simultaneously

^†^Vital signs include measurements of blood pressure, pulse, and body temperature

^‡^Laboratory assessments include the following:

• Blood chemistry tests: AST, ALT, ALP, TB, GGT, BUN, creatinine, eGFR, Na, K, Cl

• Hematology tests: WBC. RBC. hemoglobin, hematocrit, platelet count

^§^A human chorionic gonadotropin test conducted via urinalysis (only for women with the possibility of pregnancy)

### Participants

#### Inclusion criteria

Men and women aged 19–85Patients who have been diagnosed with asthma and treated for over 4 weeksPatients who are being administered ICS-LABA and LTRA or ICS and LTRAPatients who voluntarily decide to participate in this clinical trial and sign a consent form

#### Exclusion criteria

Patients with co-morbidities such as pneumonia, interstitial lung disease, and active pulmonary tuberculosis on chest X-ray examinationPatients who have been using maintenance therapy with oral steroids, anti-IgE antibodies, or herbal medicines for asthma treatment since 4 weeks ago.Patients with aspartate aminotransferase (AST)/alanine aminotransferase (ALT) levels exceeding twice the normal limit, or with an estimated glomerular filtration rate (eGFR) of less than 60 mL/min/1.73 m^2^ (However, for those aged 65 and over, individuals with an eGFR less than 45 mL/min/1.73m^2^)Chronic heart failure of class III or IV (New York Heart Association)Patients with alcohol or other substance abuse/dependency or historyPatients with malignant tumors or a history of malignant tumors (however, if they have not recurred for more than 5 years, participation is possible).Patients with a history of hypersensitivity reactions or allergies to research-related drugsPatients who are unable to read and write or have cognitive impairmentPregnant or lactating women Patients who participated in other clinical trials within recent 30 days before this clinical trial (based on the date of written consent) If the researcher determines that it is inappropriate to participate in clinical research due to other reasons

#### Withdrawal criteria

Cases where the participant received treatments that could influence the study outcomes without the researcher's instructions during the study periodCases where the participant did not adhere to the clinical trial protocol or the compliance was below 70%Cases where the participant experienced adverse reactions that made it difficult to continue the clinical trial or where severe adverse reactions occurredCases where the participant withdrew their consentCases where the participant used additional drugs or any herbal medicine that could affect asthma treatment during the clinical trial (excluding temporary short-term use for treating acute exacerbation of asthma)Cases where the LTRA prescription was changed after the participant's registrationOther reasons deemed by the researcher as inappropriate for the continuation of the clinical trial

### Randomization, allocation concealment, and blinding

Study participants will be randomly assigned in a 1:1 ratio to the intervention and control groups. Random assignment is performed by an independent statistician using SAS V.9.1.3 for Microsoft Windows (SAS Institute Inc., NC, Cary, USA) to generate random numbers and construct a random assignment table. The random number table and the intervention or placebo group assignment table created using SAS will be retained by a third party until the termination or completion of the study, with no access granted to the researchers. Written consent to participate in the study will be obtained by the principal investigator or sub-investigators, who are doctors and Korean medicine doctors authorized by the principal investigator. Once the study participants are informed about the study and have signed a consent form for participation in the clinical trial, they are assigned an institution number for each site and a screening number. After screening, suitable participants are assigned random numbers. The study participants who are finally selected to participate in the clinical trial through the screening test are given a registration number. Based on the random assignment table held by a third party, they are assigned to a group corresponding to their registration number. The manufacturers of the investigational drugs and placebos directly conduct code labeling assigned to the investigational drugs and placebos, and a third party matches the generated random numbers and codes. The investigational drugs and placebos will be stored in the clinical trial pharmacy of each institution and delivered to the clinical participants by a managing pharmacist who maintains blinding.

The investigational drug and placebo are managed using assigned codes, implementing a double-blind method, in which the researchers, outcome assessors, data analysts, and trial participants are unaware of the type of drug being administered. During the clinical trial period, if the blinding must be lifted before the completion of the clinical trial due to a serious adverse reaction, the research participant contacts a third party and proceeds with the blinding release procedure after reviewing and approving the reason for the blinding release.

### Sample size

The current study requires a total of 168 test subjects. Considering a dropout rate of 15%, the sample size will be adjusted to 198.

The required number of recruits per group was calculated with reference to the study conducted in 2019 [10]. According to the reference literature, the changes in forced expiratory volume in the first second (FEV_1_) after 8 weeks of Bufei granule administration in a total of 178 subjects, with 89 in the test group and 89 in the control group, are as follows (Table 2).

**Table 2 Tab2:** Changes in FEV_1_ (L) observed in the study by Xin X and Peng F (2019) [10]

	FEV_1_ (L) before treatment	FEV_1_ (L) after treatment
Test group (*n* = 89)	0.88 ± 0.30	1.72 ± 0.75
Control group (*n* = 89)	0.89 ± 0.25	1.37 ± 0.80

As the primary outcome of this study is the variation in FEV_1_, the calculation of FEV_1_ changes was based on the aforementioned study. The mean change in FEV_1_ in each group was calculated as the difference between the post-treatment and pre-treatment means. The standard deviation was calculated based on the following formula, considering the pre-treatment standard deviation, post-treatment standard deviation, and the correlation between measurements taken pre- and post-treatment:$$\mathrm{Mean}\;\mathrm{change}\;\mathrm{in}\;{\mathrm{FEV}}_1\;=\;\mathrm{Post}-\;\mathrm{treatment}\;\mathrm{mean}\;\;-\;\;\mathrm{Pre}-\mathrm{treatment}\;\mathrm{mean}$$$$\mathrm{Standard}\;\mathrm{deviation}\;\mathrm{of}\;{\mathrm{FEV}}_1\;\mathrm{change}\;=\;{({\mathrm{Pre}-\mathrm{treatment}\;\mathrm{standard}\;\mathrm{deviation}}^2\;+\;{\mathrm{Post}-\mathrm{treatment}\;\mathrm{standard}\;\mathrm{deviation}}^2\;-\;2\;\ast\;\mathrm{Correlation}\;\mathrm{coefficient}\;\mathrm{between}\;\mathrm{pre}-\;\mathrm{and}\;\mathrm{post}-\mathrm{treatment}\;\mathrm{measurements}\;\ast\;\mathrm{pre}-\mathrm{treatment}\;\mathrm{standard}\;\mathrm{deviation}\;\ast\;\mathrm{post}-\mathrm{treatment}\;\mathrm{standard}\;\mathrm{deviation})}^{(1/2)}$$

The correlation coefficient between the pre- and post-treatment measurements was conservatively assumed to be zero because of a lack of related references. The calculated FEV_1_ change from this reference paper was found to be 0.39 ± 0.838 for the control group and 0.84 ± 0.808 for the test group.

In this study, the primary outcome is the change in FEV_1_, with a significance level (α) set at 0.05 and a test power (1-β) set at 0.8. The number of participants was determined using g-power, considering a two-sided test and an allocation ratio of 1:1 [11]. As a result, the effect size was calculated to be 0.437, and the total number of participants was 168. Taking into account the number of recruitable participants, the minimum scope for validity assessment, and a dropout rate of 15%, the total number of participants was determined to be 198 to secure the minimum necessary sample size.

### Interventions

#### Drug interventions

The CSBHT and placebo were designed with the same weight (1.8 g/pack) and packaging. CSBHT is composed of the following main components: Rehmanniae Radix Preparata (187.5 mg), Dioscoreae Rhizoma (93.5 mg), Corni Fructus (93.5 mg), Poria Sclerotium (70.0 mg), Moutan Radicis Cortex (70.0 mg), Alismatis Rhizoma (70.0 mg), Schisandrae Fructus (70.0 mg), Ponciri Fructus Immaturus (70.0 mg), Liriopis seu Ophiopogonis Tuber (70.0 mg), Asparagi Tuber (70.0 mg), Fritillariae Thunbergii Bulbus (70.0 mg), Platycodonis Radix (70.0 mg), Coptidis Rhizoma (70.0 mg), Armeniacae Semen (70.0 mg), Pinelliae Tuber (70.0 mg), Trichosanthis Semen (70.0 mg), Scutellariae Radix (70.0 mg), and Glycyrrhizae Radix et Rhizoma (23.25 mg). The placebo is similar to CSBHT in appearance, taste, and smell, but does not contain any active ingredients. It comprises lactose (252.0 mg), corn starch (1030.0 mg), PEG6000 (233.0 mg), gum arabic (140.0 mg), HPC-M (80.0 mg), CMC-na (40.0 mg), yellow iron oxide (0.4 mg), black iron oxide (0.4 mg), red iron oxide (0.2 mg), caramel color (12 mg), and Opadry Brown amb2 (12 mg). Both CSBHT and the placebo are produced by Hanpung Pharmaceuticals, according to the pill section of the General Rules of Formulation in the Korean Pharmacopoeia. The intervention and control groups will take either the herbal compound CSBHT or the CSBHT placebo, both of which are in pill form, at a dose of 1.8 g/pack, three times a day for a total of eight weeks. They will visit 0, 4, and 8 weeks after the screening visit, receiving a total of two prescriptions at 0 and 4 weeks, respectively. At each visit, evaluations included in this study, including any adverse reactions, will be conducted. Compliance with medication is defined as the amount of clinical trial medication completed during the clinical trial period divided by the total amount to be taken; and if this value is < 70%, they will be dropped from the study.

$$Compliance\mathit\;(\%)\mathit=\mathit\;\frac{\mathit D\mathit o\mathit s\mathit a\mathit g\mathit e\mathit\;\mathit a\mathit d\mathit m\mathit i\mathit n\mathit i\mathit s\mathit t\mathit e\mathit r\mathit e\mathit d}{\mathit D\mathit o\mathit s\mathit a\mathit g\mathit e\mathit\;\mathit p\mathit l\mathit a\mathit n\mathit n\mathit e\mathit d}\mathit\;\times\;100$$

$$Dosage\;administered=Dosage\;prescribed\;-\;Dosage\;returned$$

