### Outcome measurements

#### Primary outcome

##### Pulmonary function test (Forced Expiratory Volume in 1 s, FEV_1_)

Spirometry is a test that plays an essential role in the diagnosis and monitoring of asthma to identify airflow limitation [2]. Using spirometry, measurements of forced vital capacity (FVC), FEV_1_, among others are taken, and changes in FEV_1_% and liters are observed to measure the amount of change. The primary outcome of this study will be the average change in FEV_1_ scores between baseline and week 8.

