### Statistical analysis

#### Effectiveness outcomes

Statistical analyses are conducted independently by a statistical expert using SAS. In the two-tailed tests, the level of significance is set at 0.05. All analyses primarily utilize intention-to-treat analysis, with per-protocol analysis conducted concurrently, and the results are presented together. In the demographic baseline data, continuous variables are presented as mean and standard deviation and are analyzed using an independent t-test or Mann–Whitney U test. Categorical variables are presented as frequency and proportion and analyzed using a chi-square test or Fisher's exact test (when the expected frequency is less than 5 in more than 25% of all values).

The primary efficacy evaluation is based on the mean change in FEV_1_ scores evaluated at week 8 (56 days post-dosing), whereas secondary efficacy evaluations compare the means of PEF, FVC, FEF25–75, FeNO, ACT scores, AQLQ scores, Serum IgE, eosinophil count, CRP, and the frequency of rescue medication use assessed at baseline and weeks 4 and 8. If the assumption of normality is satisfied, an independent t-test is conducted; otherwise, the Mann–Whitney U test is applied. However, if significant differences between the groups are found in baseline values, an analysis of covariance (ANCOVA) is performed. Missing data is replaced using the last observation carried forward method; each missing value is replaced with the participant's last observed value. For the secondary efficacy evaluation, the distribution of participants according to each diagnosis of Korean medicine pattern identification assessed at baseline is presented as frequency and proportion and visualized in tables or graphs through descriptive analysis.

Subgroup analysis will be performed according to the following criteria: First, subgroups will be divided according to the type of asthma medication (ICS or ICS + LABA) taken in addition to the LTRA at enrollment. Second, the effect will be further analyzed by age, separating younger patients (< 35 years) from older patients (> 60 years). Third, subgroups will be defined as male and female. Fourth, subgroups will be created based on severity as measured by ACT, ≤ 15 and > 15. Finally, subgroup analyses will be performed according to Korean medicine pattern identification.

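### Withdrawing participants for low compliance, protocol deviation, added drugs or an LTRA change is not reconciled with the intention-to-treat primary analysis

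*Protocol article*

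**What the plan says.** All references are to the protocol article.

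- **Drug interventions** defines compliance as "the amount of clinical trial medication completed during the clinical trial period divided by the total amount to be taken" and adds "if this value is < 70%, they will be dropped from the study".
- **Withdrawal criteria** repeats the 70% threshold. It also lists failure to follow the protocol, additional drugs or herbal medicines that could affect asthma treatment (brief use for an acute exacerbation is exempt), and "Cases where the LTRA prescription was changed after the" participant's registration. Withdrawal of consent stands in the same list, with no distinction between kinds of withdrawal.
- **Concomitant medications** halts the trial for a participant whose asthma keeps worsening and who needs continuous additional medication.
- **Effectiveness outcomes** states: "All analyses primarily utilize intention-to-treat analysis, with per-protocol analysis conducted concurrently". It also states: "Missing data is replaced using the last observation carried forward method".
- **Primary outcome** is "the average change in FEV_1_ scores between baseline and week 8".

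**The concern.** An intention-to-treat comparison needs the outcome of every randomised participant, whatever their adherence. The rules above end participation because of events that arise after randomisation and that treatment can influence. Low compliance may reflect tolerability, and an LTRA change or an added asthma drug may reflect poor control. The Safety analysis section itself expects dropouts from treatment failure and adverse reactions.

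If removal differs between arms, or is related to outcome, the week-8 contrast is no longer purely the randomised one. Missing values are then created by the protocol itself, and FEV1 that was never measured cannot be recovered at analysis.

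**Working it through.** **1. Timing of the 70% rule.** Compliance is measured over the whole dosing period from returned packs, so its final value is known around week 8. Someone who took under 40% of the first half is certain to fail earlier (0.5 × 0.40 + 0.5 × 1 = 0.70). For everyone else the rule takes effect when the primary outcome is due or already measured. At that point it cannot work as a treatment-stopping rule; it can only exclude from analysis.

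**2. Withdrawals before week 8.** The article describes no week-8 FEV1 for these participants. Under the stated missing-data rule, the value used is an earlier one: baseline, or week 4 if FEV1 was recorded with the other spirometry.

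**3. The plan's own figures.** With a pre–post correlation of zero, the SDs of change are √(0.25² + 0.80²) = 0.838 and √(0.30² + 0.75²) = 0.808, pooled 0.823. From Table 2 the control change is 1.37 − 0.89 = 0.48 and the test change is 0.84. The effect size is (0.84 − 0.48)/0.823 = 0.437. At "a significance level (α) set at 0.05 and a test power (1-β) set at 0.8", two-sided, the t-test needs 84 per arm, or 168 in total, and 168/0.85 rounds up to 198. The stated size reproduces. The text prints 0.39 for the control change, which disagrees with Table 2; that is a separate matter, and 0.48 is the value behind 168.

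**4. Illustration with no true effect.** Assumptions: 99 per arm; SD s = 0.82 L in both arms; a fraction q removed from one arm only; those removed average k SDs below the arm mean; mean change μ in both arms.

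- Deletion: shift = q·k·s/(1 − q), leaving 99(1 − q) in that arm.
- Baseline carried forward (change = 0): shift = (1 − q)[μ + q·k·s/(1 − q)] − μ = q(k·s − μ), with 99 in each arm.
- Type I error: noncentral t with noncentrality shift/[s√(1/n₁ + 1/n₂)].

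For k = 1:

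| Handling | Shift (L) at q = 5 / 10 / 15% | Two-sided type I error |
|---|---|---|
| Baseline carried forward, μ = 0.48 | 0.017 / 0.034 / 0.051 | 5.2 / 6.0 / 7.2% |
| Baseline carried forward, μ = 0 | 0.041 / 0.082 / 0.123 | 6.4 / 11 / 18% |
| Deletion | 0.043 / 0.091 / 0.145 | 6.5 / 12 / 22% |

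Example, row 1 at 10%: 0.10 × (0.82 − 0.48) = 0.034, and 0.034/(0.82 × √(2/99)) = 0.29, which gives 6.0%.

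For k = 0.5, deletion gives 5.4–9.1%. Carrying baseline forward with μ = 0.48 reverses the sign, since 0.41 − 0.48 is negative, and the error stays about 5%. Deletion of 10% against 5% (k = 1) gives 6.8%. Equal removal in both arms gives about 5%.

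**5. Direction and power.** Suppose those removed are otherwise average (k = 0), both arms improve by 0.48 L, and removal is 15% against 5%. Carrying baseline forward then creates a difference of 0.10 × 0.48 = 0.048 L, whose sign depends on which arm loses more. With 15% removed equally, the planned 0.36 L shrinks to 0.85 × 0.36 = 0.306 L. The SD becomes about 0.797 L and power 0.766, against 0.864 with all 99 per arm observed.

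**The case against.** The strongest reply is that nothing in the article takes withdrawn participants out of the intention-to-treat set or discards a measured week-8 value. That is correct. A reader might infer a direct contradiction, with outcome data deleted from the primary analysis, but the document does not say so. If the 70% rule takes effect after week-8 spirometry, an intention-to-treat analysis as stated would use that value. The conflict is with the principle, plus a real loss of data for withdrawals before week 8.

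A reader might also take 12% or 22% as the size of the problem. Those figures need deletion from one arm only, whereas the plan carries values forward. Under that rule and the plan's own 0.48 L control change, the inflation is small.

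Nor does the planned 15% dropout support the 15% scenario: it is all-cause and covers both arms, and it is not a rate for these rules.

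Finally, the article condenses a fuller protocol and its schedule table is not shown, so off-treatment visits may be described elsewhere. That limits what can be said about absent detail. It does not remove the point, because the article itself states both the withdrawal rules and the intention-to-treat analysis and leaves them unreconciled.

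**Conclusion.** The point holds in a limited form. The withdrawal rules do not separate stopping study medication from leaving follow-up, and for these reasons that conflicts with the principle of the intention-to-treat primary analysis. Early withdrawals lose their true week-8 FEV1, and the 70% criterion is in effect a per-protocol criterion written as study withdrawal.

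Bias may run either way, and its size cannot be fixed from the documents. Under the one-arm, 1-SD assumptions it ranges from slight, when baseline is carried forward with a 0.48 L mean change, to substantial under deletion or with no mean change. Balanced removal leaves the type I error at about 5% but can cost power. The drop rates and the deficit in those removed are assumptions throughout. The sample size is not in question.

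**What to change.** Reconcile Withdrawal criteria, Drug interventions, Concomitant medications and Effectiveness outcomes on outcome follow-up only:

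- State that, except where consent to follow-up is withdrawn, every randomised participant has the already scheduled week-4 and week-8 spirometry, whether or not study medication was stopped.
- State that all observed values are used in the intention-to-treat analysis.
- State that compliance below 70%, protocol deviation, added drugs and an LTRA change define exclusion from the per-protocol set, and are not reasons to end outcome follow-up or discard data.

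The clinical rules on stopping treatment, including the halt under Concomitant medications, stay as they are. The total stays at 198. With all 99 per arm observed, power at 0.437 is 0.864; this is an upper bound, because non-adherent participants may dilute the effect. The cost is a wording change, and some participants off study medication attending visits already scheduled.
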